#### Mental health assessment

The validated Patient Health Questionnaire (PHQ-9) and Generalised Anxiety Disorder (GAD-7) scale will be used to assess the prevalence of depression and anxiety, respectively.

The PHQ-9 is a 9-item self-report screening tool for depression. Each item is rated on a 4-point scale from 0 to 3 (0 = never, 1 = several days, 2 = more than half the time, and 3 = nearly every day). The overall scores range from 0 to 27, with higher scores indicating greater symptom severity. Scores 5, 10, 15, and 20 represent cut-offs for mild, moderate, moderately severe, and severe depression, respectively. The PHQ-9 has a sensitivity of 88% and a specificity of 88% for detecting depression [20].

The GAD-7 is a 7-item self-report screening tool for anxiety. Each item is rated on a 4-point scale from 0 to 3 (0 = never, 1 = several days, 2 = more than half the time, and 3 = nearly every day). The overall scores range from 0 to 21, with higher scores indicating greater symptom severity. Scores 5, 10, and 15 represent cut-offs for mild, moderate, and severe anxiety, respectively. The GAD-7 has a sensitivity of 89% and a specificity of 82% for detecting anxiety [21].

### Intervention

The Freedom from Diabetes protocol is a comprehensive one-year ILI focused on four key components: dietary modifications, physical activity, psychological support, and medical management. Each participant is supported by a dedicated team of experts, which includes a physician, a dietitian, a physical therapist/certified yoga professional, a psychologist, a mentor (who is a past participant volunteering to guide the new participant), and a monitor (for follow-ups and reminders for lab tests and appointments). Participants also have access to a mobile application that facilitates communication with the team via voice/video calls and text messages.

The interventions implemented in the DIRemI study are shown in Fig 2. The four protocols are divided into several phases, each designed to introduce incremental modifications, initially focusing on diet and exercise. Subsequently, both are enhanced by the addition of emotional stress release and goal setting. The ultimate objective of the phases is to render the participants self-sufficient and able to sustain the changes. Progression to the subsequent phase is contingent on achieving the predetermined target for the previous phase. The goals for each phase of the program are established collaboratively with the patient’s healthcare team, which comprises a dedicated physician, dietitian, and physical therapist. Throughout the program, these objectives serve as a guide for patient progress and are periodically reviewed and adjusted as necessary.

**Fig 2 pone.0306394.g002:**
[figure not shown]
DiRemI intervention.

#### Dietary modifications

Dietary intervention is focused on a plant-based diet, individualised based on the BMI and associated medical conditions of the participants. The four distinct phases of dietary intervention are adjustment, accelerated weight loss, muscle building, and maintenance. As part of the dietary intervention, participants are primarily introduced to consuming greens, lentil-based food items, sprouts, and vegetable salads. Soaked nuts such as walnuts, almonds, seeds, and fruits are also recommended for consumption, based on individual blood sugar levels. Sample diet charts are included in the supplementary file (S2 Appendix).

Phases 1 and 2 primarily focus on weight loss through adjustment to a plant-based alkaline diet which helps reduce inflammation. Consumption of milk and milk products, meat, eggs, and poultry are restricted during these phases. In Phase 1, the focus is on a shift from the usual high-carbohydrate unbalanced diet to a balanced diet considering all macro-and micronutrients by increasing the consumption of cooked and raw vegetables along with green smoothies, providing a rich variety of antioxidants and phytonutrients. The reported average calorie intake for Indian T2D patients is 1547 kcal (95% CI 1486 to 1608) and constitutes 64% of the total energy intake [22]. The average calorie intake for Phase 1 is reduced to 1200–1400 kcal/day. In the second phase, one month of intermittent fasting and juice fasting is recommended to aid in faster weight loss and detoxification [23], depending on the BMI of the participant; those already achieving a normal BMI (<23 kg/m^2^) do not undergo intermittent fasting but only juice fasting. The intermittent fasting and juice fasting protocols are described in Fig 3. The average calorie intake during this period ranges from 300–500 kcal on days of juice fasting to 400–500 kcal on single-meal days; the average intake is 800–1000 kcal for days when two meals are consumed. The recipes for juices used in juice fasting (red, white, and green) have been previously described [24]. During periods of fasting, the participants are instructed to closely monitor and report their sugar levels to their assigned physician through a mobile application and accordingly, drug-dose adjustments are done.

**Fig 3 pone.0306394.g003:**
[figure not shown]
Intermittent fasting protocol: 3, all three meals; 2, Brunch/Lunch and Dinner; 1, Brunch/Lunch or Dinner; 1(D), Dinner only; JF, Juice fasting.

Once the target BMI (based on the initial goal setting-23-25 kg/m^2^ or a 3–5 point drop) is achieved, calorie intake is gradually increased to 1400–1600 kcal to facilitate muscle building in Phase 3. In addition, protein intake is increased to 75–80 grams depending on the intensity of the recommended exercises. The focus here is on building up muscle mass and increasing stamina. The last phase emphasises on maintenance diet. In this phase, once the blood sugar levels have stabilised, other food items restricted from the regular diet are reintroduced phase-wise under the close supervision of the dietitian. This helps participants to understand the portion and frequency control required to sustain the results. This phase also helps participants maintain good glycemic control despite the reintroduction of restricted foods. Based on the chosen long-term exercise plan, calorie intake may be increased to 1600–1800 kcal/d (for those who no longer need to lose further weight). This phase is designed to enable individuals to effectively manage their diet and sustain an exercise plan for better glycemic control, while maintaining weight loss post-intervention without support.

During each phase, the blood sugar levels are closely monitored.

#### Physical activity modifications

The phase-wise physical activity protocol is shown in Fig 2. The exercises primarily focus on building and sustaining strength, flexibility, and stamina in the long run by adopting a 3-2-1 pattern per week (three days for strength, two days for flexibility, and one day for stamina exercises) over one year. The exercise duration is 30–45 minutes per day, 6 days a week. Sample exercise plans are included in the supplementary file (S2 Appendix).

Phase 1 exercises aim to promote blood circulation, muscle activation, and anti-gravity exercises to enhance post-meal glycemic control [25]. Additionally, exercises focused on improving posture, breathing, flexibility (yoga), and strength are recommended. Based on the progress made during Phase 1, the activities for Phase 2 are recommended from the following five categories: muscle gain, weight loss, core strengthening, yoga, and specialised exercises for senior participants. This phase focuses on strengthening the upper and lower limb muscles and improving flexibility, cardiopulmonary endurance, balance, and coordination in addition to weight loss. The third phase of the intervention focuses on individualised athletic specialisation based on age, BMI, and preference by increasing the intensity and duration of the selected exercise form. Solo exercises such as weight training, swimming, running, cycling, and yoga, are suggested. To establish a consistent state of fitness and sustenance after the completion of the program, the final phase focuses on periodized exercise plans for managing various goals and activities, enabling the participant to independently create and design a personal workout plan for the following week, month, and year.

#### Psychological support

The third protocol of psychological intervention is designed to address stress and anxiety levels by raising awareness of the mind-body connection. At baseline, all participants will be assessed for depression and anxiety using validated tools: the Participant Health Questionnaire (PHQ) and Generalised Anxiety Disorder (GAD) scale. Those who exhibit moderate to severe anxiety and/or depression are referred to in-house psychologists for one-on-one counseling sessions tailored to their individual needs. Drawing from a range of therapeutic techniques, including Cognitive Behaviour Therapy (CBT), Rational Emotive Behaviour Therapy (REBT), Neuro-Linguistic Programming (NLP), Clinical Hypnotherapy, Life Coaching, Pranic Healing, and Eclectic Therapy, therapists work to meet the unique needs of each participant.

All participants, regardless of their anxiety and depression scores, attend 56 days of group therapy sessions during the one year; these incorporate guided meditation and journaling. The intervention is centred on cultivating positive energy through principles such as the law of attraction, gratitude, and affirmation [26]. Engaging in cognitive activities, such as creating a vision board, serves as a proactive measure for achieving personal goals and enhancing emotional intelligence [26, 27]. The intervention also emphasises the importance of long-term health management and maintenance through online group sessions following the program.

At the end of 6 months, the PHQ and GAD are re-administered to assess the improvement in the mental health outcomes.

#### Medical management

The primary focus of medical management is to closely monitor participants during the intervention. The assigned physician is accountable for evaluating the participant’s health condition at the outset by considering a comprehensive medical history of diabetes, its potential complications, and any co-existing conditions, along with biochemical analysis of the parameters listed previously. Following the correction of micronutrient deficiencies, if any, the physician adjusts the medication dosage according to the participant’s weight, BMI, and daily self-reported blood sugar level (BSL) through the mobile application. Once blood sugar levels are stabilised, participants are asked to report them less frequently (weekly/fortnightly). The physician considers the participant’s history of comorbidities for further management and maintains strict control over the HbA1c levels throughout the year. In addition to daily dosage modifications, the physician is required to conduct at least three medical consultations with the participant throughout the one-year program.

#### Mode of delivery

The intervention is delivered online through video meetings and conferences. Throughout the year, the team of experts keep in touch with the participants through an average of 63 calls per year. In addition to the 12 monthly sessions, group sessions covering the primary focus for that month, additional group activities such as mid-month catch-up sessions, and diet/exercise-wiser sessions are conducted to check and improve adherence and motivation. Participants have access to a dedicated mobile application to communicate with their team and regularly track and update their vitals (fasting and postprandial blood sugar levels, weight, and blood pressure) along with their diet and exercise regimen. Participants are also provided with region-specific plant-based recipes to avoid drastic changes in their existing diet.

For exercise recommendations, fitness level, age, physical limitations, and preferences are considered. Phases 1 and 2 have pre-recorded exercise sessions which are relayed in the morning and evening for six months, catering to differing needs. Additionally, other exercise videos for different physical limitations like spondylosis, frozen shoulder, and knee issues that are provided based on the requirement and recommendation. The participants are guided individually by their assigned physical therapist.

Overall, diet, physical activity, and stress management are tailored to each participant’s individual needs, considering their comorbidities, age, sex, and fitness levels. In total, there are 600+ exercise videos, session videos, meditation audios, PDFs, and 400+ recipes to choose from, giving the participants variety and progression.

#### Adherence check

Participants in the program are regularly encouraged to follow the protocol, and their adherence is assessed through monthly checks using a mobile application. These checks involve short multiple-choice questionnaires designed to evaluate participants’ adherence to the relevant interventions for that period. The monthly adherence scores are calculated and used to provide feedback to experts, who can then take appropriate action. At the end of the 12-month intervention period, monthly scores are combined to generate an overall adherence score for each participant. The purpose of these measures is to ensure that participants adhere to the program’s protocol and provide feedback to experts for any necessary actions.

### Control group (Routine medical care)

The control group will receive routine medical care along with education for management of T2D and its associated comorbidities based on current clinical guidelines.

### Outcome measures

The primary outcome measures are a) Weight loss of more than or equal to 10% and b) Remission of T2D (HbA1c less than 6.5% for at least 3 months without medication). Secondary outcomes include a) reduction in dosage and/ or frequency/ class of drug or complete stoppage of diabetes medication, b) improved glycemic control (HbA1c less than 7% with or without medication), c) reduction in fasting glucose levels (below 126 mg/dl) and PP blood glucose levels (below 200 mg/dl) with or without glucose-lowering medications), d) improvement in diabetes-related complications (nephropathy- improvement in terms of eGFR>90 mL/min/1.73m^2^), e) improvement in comorbidities (hypertension- blood pressure ≤140/90 and dyslipidaemia- Total cholesterol <200 mg/dl, triglycerides <150 mg/dl, and HDL >40 mg/dl for males and >50 mg/dl for females), and f) improvement in mental health outcomes (anxiety and depression- Reduction in the score—below 10).

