### Sample size determination

We calculated the sample size for our study using Bonferroni correction to adjust for two primary outcome measures: weight and HbA1c. With an overall alpha level of 0.05, the adjusted significance level for each outcome was set to 0.025. Assuming a power of 95%, the required sample sizes were determined based on Cohen’s d effect sizes of 0.445 for weight and 0.635 for HbA1c, based on a previous study by Lean et al. (2018) [18]. The calculations indicated a sample size of 132 participants per group for weight and 65 participants per group for HbA1c level. To ensure adequate power for both outcomes, we selected the larger sample size requirement, resulting in a total sample size of 132 participants per group. To account for the potential dropout and loss to follow-up of 30%, the final sample size was estimated at 360 (180 in each group).

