### Statistical analyses

Primary outcome measures will be analysed using two-sided statistical tests with a type I error rate of α = 0.05. Primary analysis will be performed using the intention-to-treat method. Categorical data will be compared between the two groups using chi-square or Fisher’s exact tests. Continuous data will be evaluated using parametric or non-parametric tests based on data distribution.

For outliers (± 3 standard deviation), efforts will be made to cross-check and obtain the correct values. Failing this, the case will be considered as missing data. In the case of random missing values, two separate analyses will be performed: one including the cases with missing data by choosing pairwise deletion and the other excluding it using listwise or case-wise deletion. A complete case analysis will be considered if differences are observed between the two analyses. In the case of non-random missing values, the imputation method may be used by replacing the missing value with the mean for that variable.

Potential adjustments for baseline values, age, gender, and disease duration may be considered. Multivariable linear and logistic regression analyses will be used to determine predictors of remission. Finally, subgroup analyses may be performed based on factors such as gender, age, comorbidity, diagnosis length, and severity to investigate potential variations in treatment responses.

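### The stated 95% power is for mean differences in weight and HbA1c, but both primary outcomes are yes/no thresholds, so neither has a power statement.

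*Protocol article*

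**What the plan says.** **Sample size determination.** The calculation is made "using Bonferroni correction to adjust for two primary outcome measures: weight and HbA1c". For each outcome, "the adjusted significance level for each outcome was set to 0.025". Power is set at 95%, with "Cohen’s d effect sizes of 0.445 for weight and 0.635 for HbA1c". This gives 132 per group for weight and 65 for HbA1c. The larger figure is taken and raised to 180 per group for 30% loss.

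**Outcome measures.** "The primary outcome measures are a) Weight loss of more than or equal to 10% and b) Remission of T2D", where remission is HbA1c under 6.5% held for at least 3 months without medication. The specific objectives, described as those given at ethics submission, use the same 10% cut and a drug-free HbA1c below 6.5%.

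**Statistical analyses.** "Categorical data will be compared between the two groups using chi-square" or Fisher's exact tests. Continuous data go to parametric or non-parametric tests.

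The article gives no expected proportion for either endpoint in either group.

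**The concern.** The two sections describe different primary outcomes. One has mean weight and mean HbA1c; the other has the share of participants past a threshold. A standardised mean difference does not by itself give the power of a comparison of proportions. That also depends on where the threshold falls in the control distribution and on the spread in each arm.

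For remission the gap is wider. A participant must be off medication as well as below 6.5%, and the programme adjusts and tapers drugs as it goes. HbA1c can fall while drugs continue, and drugs can be stopped with little change in HbA1c. No cut on HbA1c alone turns d = 0.635 into a difference in remission rates.

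Two things are at stake. A reader who takes 95% as the power for the primary endpoints has no basis for it. And while the two sections disagree about what is primary, a result could be presented as mean change or as responders.

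**Working it through.** **Inputs from the article:** d = 0.445 and 0.635; power 0.95; 0.025 per outcome; 132 and 65 per group; 180 per group enrolled; 30% loss. **Assumed, because the article does not give them:** control rates, and the SD in each arm.

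**1. Reproducing the stated figures.** For two means, n per group ≈ 2(z₁₋α/₂ + z₀.₉₅)² / d².

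- Two-sided 0.05 (the same as one-sided 0.025), d = 0.445: 2(1.960 + 1.645)² / 0.445² = 131.2; with the t distribution, 132.2.
- Same level, d = 0.635: 64.5; with the t distribution, 65.4.

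These match 132 and 65, so the 95% refers to a comparison of means. (At two-sided 0.025 the t-test needs 154 and 77. That is a separate point.)

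**2. Cutting d = 0.445 at a threshold, equal SDs.** Let pC be the control proportion reaching the cut. For a normal outcome, pT = 1 − Φ(z₁₋pC − 0.445). Power is that of the pooled two-proportion test: Φ{[(pT − pC)√n − z₁₋α/₂√(2p̄(1 − p̄))] / √[pC(1 − pC) + pT(1 − pT)]}, with p̄ = (pC + pT)/2, n = 132 and two-sided α = 0.025.

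| Control rate | Implied intervention rate | Power |
|---|---|---|
| 5% | 11.5% | 37% |
| 10% | 20.1% | 53% |
| 20% | 34.6% | 66% |

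The same mechanical cut with d = 0.635 gives 73%, 88% and 95%. For remission this is an illustration only, since it ignores the medication condition.

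**3. Same d, unequal SDs.** Suppose the intervention SD is 1.5 times the control SD and d is on the pooled SD. In control-SD units the shift is 0.445 × √[(1 + 1.5²)/2] = 0.567, and pT = 1 − Φ[(z₁₋pC − 0.567)/1.5].

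| Control rate | Implied intervention rate | Power, n = 132 | Power, n = 126 |
|---|---|---|---|
| 5% | 24% | 98% | 98% |
| 10% | 32% | 99% | 98% |
| 20% | 43% | 96% | 96% |

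With 126 per group and a 5% control rate, the same d therefore gives 36% power with equal SDs and 98% with this SD ratio.

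**4. What the trial can detect in proportions.** Expected evaluable number: 180 × 0.7 = 126 per group. At two-sided 0.025 and 90% power:

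| Assumed control rate | Detectable intervention rate |
|---|---|
| 5% | 19.4% |
| 10% | 27.1% |
| 20% | 40.2% |

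**The case against.** **A reader might infer that the trial is underpowered.** The article does not support this. The low figures in step 2 need a normal outcome with equal SDs, and no SD is given. A wider spread under an intensive programme than under routine care is plausible, and step 3 shows that it can restore the power. The article also speaks of weight, not percent change; if d refers to attained weight, it does not map to a percent-loss cut at all. And 126 per group may suffice if the true differences are large. This objection stands: the supportable claim is that the power is unknown.

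**A reader might infer that the 10% cut contradicts the programme's BMI target.** It does not. The dietary section's wording, "Once the target BMI (based on the initial goal setting", introduces the condition for moving to Phase 3. It does not define an endpoint, and the objectives and outcome measures agree on 10%.

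**A reader might conclude that percent weight change should become primary because the trial was sized for it.** The sample size section mentions neither percent change nor a baseline-adjusted analysis. The thresholds were set at ethics submission, the trial is prospectively registered, and recruitment opened on 1 March 2024. Changing the primary outcome of an open-label trial at this stage is hard to justify, and the problem does not require it.

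**The analysis section does not assign a test to each primary outcome, and an unseen analysis plan may do so.** That is fair, but it leaves the conflict in place: this article states both the sizing basis and the outcome definitions, and they differ.

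**Conclusion.** The point holds as a mismatch between the sample size and the primary outcomes. The 95% power is for differences in mean weight and mean HbA1c; the primary outcomes are two proportions, and no power is stated for them. This needs no outside figure, because 132 and 65 reproduce exactly as comparisons of means.

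The size of the discrepancy cannot be fixed from the article. For weight it runs from about 37% power (5% control rate, equal SDs) to above 95% (intervention SD 1.5 times the control SD), all at 132 per group and two-sided 0.025 with assumed control rates. For remission no conversion is possible. The mismatch in itself biases neither the treatment estimate nor the type I error rate. What is wrong is the power claim and the unclear statement of what is primary.

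**What to change.** Keep both binary primary outcomes and the enrolled size. In the sample size section:

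- name the primary outcomes as the outcome measures section defines them;
- replace the power statement based on Cohen's d with the differences in proportions that the expected evaluable number can detect at two-sided 0.025. With 126 per group and 90% power these are about 5% vs 19%, 10% vs 27% or 20% vs 40%;
- label the control rates as assumptions, and state them separately for weight loss and for remission.

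Report mean percent weight change and mean HbA1c change, both adjusted for baseline, as supporting analyses. They use the continuous information without displacing the primary outcomes.

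**Cost:** a wording amendment before analysis and no added patients. The stated power becomes less favourable: the 95% claim gives way to about 90% for differences of roughly 14 to 20 percentage points.

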### Setting and eligibility criteria

The proposed study will be conducted at the Freedom from Diabetes Clinic, which operates on an online subscription-based model of 1-year duration for the management of diabetes (intervention group). Additionally, the study will include participants from two private clinics in Pune and Ahmedabad (India) (Control Group), which provide standard medical care based on established guidelines for individuals with diabetes. All individuals with T2D who enrol in these centres between March and August 2024 and meet the eligibility criteria will be recruited for this study Table 1.

**Table 1 pone.0306394.t001:** Eligibility criteria for the DiRemI study.

Inclusion Criteria	Exclusion Criteria
Age between 30 and 70 years	Pancreatitis or drug-induced diabetes (Steroids)
Confirmed diagnosis of type 2 diabetes, which may be managed with oral hypoglycemic agents, insulin, Ayurvedic antidiabetic medications, or have an HbA1c level of ≥ 48 mmol/mol (6.5%) with or without medication	Other types of diabetes (type 1 diabetes mellitus, diabetes insipidus, maturity-onset diabetes of the young, latent autoimmune diabetes in adults, or Gestational Diabetes)
Body mass index (BMI) between 25 kg/m^2^ and 35 kg/m^2^	Advanced complications related to nephropathy (eGFR<30 mL/min/1.73 m^2^, urine microalbumin >1000 mg), retinopathy (severe non-proliferative diabetic retinopathy and proliferative diabetic retinopathy), neuropathy (peripheral artery disease or diabetic neuropathy resulting in complete numbness and loss of sensation, amputations, ulcers, foot deformities, Charcot’s foot)
Duration of type 2 diabetes less than 15 years	History of heart attack, cardiac arrhythmia, bypass or stent placement surgery, ischemic heart disease, angina (class II or III), myocardial infarction within the previous 6 months, reported ejection fraction <40%, abnormal ECG, and positive stress test results (moderate or severe)
Ready to provide written informed consent	Known history of cancer
Agree to undergo the examination, lifestyle intervention program, and post-program evaluation	Pregnant and lactating women
Well-oriented in time, space, and as a person	Patients who have required hospitalization for any diabetes-related complications in the last 6 months or for depression or are on antipsychotic drugs

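### Secondary outcome b scores a follow-up level as improvement with no baseline condition, and c to f do not clearly exclude people already at target, so a baseline difference between clinics can appear as a programme effect

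*Protocol article*

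**What the plan says.** All references are to the protocol article.

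*Outcome measures* lists six secondary outcomes.
- **a** (cutting or stopping diabetes medication) is a true change from baseline and is not at issue.
- **b** is "improved glycemic control (HbA1c less than 7% with or without medication", a level with no baseline condition.
- **c** is "reduction in fasting glucose levels (below 126 mg/dl", with a similar cut-off of 200 mg/dl for post-meal glucose.
- **d** is "nephropathy- improvement in terms of eGFR>90 mL/min/1.73m^2".
- **e** begins "improvement in comorbidities (hypertension- blood pressure ≤140/90 and dyslipidaemia- Total cholesterol <200 mg/dl" and goes on to triglyceride and HDL cut-offs.
- **f** is "anxiety and depression- Reduction in the score—below 10".

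*Setting and eligibility criteria*, Table 1, admits people with "Confirmed diagnosis of type 2 diabetes, which may be managed with oral hypoglycemic agents, insulin, Ayurvedic antidiabetic medications, or have an HbA1c level" of at least 6.5%. The two routes are joined by *or*, so medicated patients need no minimum HbA1c. For kidney function the table excludes eGFR below 30 and sets no upper limit. It sets no entry threshold for blood pressure, lipids, PHQ-9 or GAD-7.

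*Statistical analyses* says "Categorical data will be compared between the two groups using chi-square" or Fisher's exact test. The same section lists baseline values, age, gender and disease duration as adjustments that might be made, without committing to any of them. It also provides for tests of continuous data.

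Groups are formed by clinic: one subscription programme against two private clinics. The design is called matched, but *Sampling and recruitment process* describes only random selection from lists of eligible patients and names no matching variable.

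**The concern.** A responder outcome labelled as improvement should not be met by someone who was at target on entry and has not moved. Outcome b can be met in that way. Under d and e the reader cannot tell whether the denominator is everyone or only those off target at entry. If it is everyone, an eGFR that falls from 110 to 92 would be scored as improvement. Under c and f, a trivial fall in someone already below the cut-off is enough.

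In a randomised trial this would mostly dilute the effect, because the share at target at entry would be equal in expectation. Here the groups are different clinics, so that share may differ systematically. An unadjusted comparison of follow-up status then carries the baseline difference into the result, as apparent benefit or harm depending on its direction.

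**Working it through.** **Inputs from the article.** 180 per group and 30% dropout (*Sample size determination*), so 180 × 0.70 = 126 per group with follow-up. The article gives no share at target at baseline and no figure of its own on this point, so there is nothing to reproduce. The 5% two-sided level is taken from the primary analysis, because none is stated for secondary outcomes.

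**Step 1: can people already at target enter?** For outcome b, yes, by either route. A medicated patient qualifies at any HbA1c, and the other route opens at 6.5%, so 6.5% to 6.9% is both eligible and below 7%. For c to f, Table 1 sets no entry value that would exclude people already inside the cut-offs.

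**Step 2: what does the unadjusted test do when the treatment does nothing?** Let p0 and p1 be the expected proportions meeting the threshold at follow-up, d = p1 − p0, pbar = (p0 + p1)/2 and n = 126.
- SE under the null: SE0 = √[2 · pbar · (1 − pbar)/n]
- SE under the actual proportions: SE1 = √[(p0(1 − p0) + p1(1 − p1))/n]
- Critical difference: c = 1.96 · SE0
- P(reject) = 1 − Φ((c − d)/SE1) + Φ((−c − d)/SE1)

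*Case A: nobody changes status; 30% vs 45% at target at entry (assumed).*
- d = 0.15 and pbar = 0.375
- SE0 = √(2 × 0.375 × 0.625/126) = 0.0610
- SE1 = √((0.21 + 0.2475)/126) = 0.0603
- c = 0.1195
- At the expected proportions, z = 0.15/0.0610 = 2.46 and p = 0.014
- P(reject) = 0.693

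*Case B: same entry shares; in both groups 90% of those at target stay there and 20% of the others reach it (assumed).*
- p0 = 0.30 × 0.9 + 0.70 × 0.2 = 0.410
- p1 = 0.45 × 0.9 + 0.55 × 0.2 = 0.515
- d = 0.105, SE0 = 0.0628, SE1 = 0.0625, c = 0.1231
- P(reject) = 0.386

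**Step 3: range over the assumed imbalance, n = 126 per group, no treatment effect.**

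| At target at entry | P(p < 0.05), no change of status | P(p < 0.05), 90% stay and 20% reach |
|---|---|---|
| 30% vs 30% | 5% | 5% |
| 30% vs 35% | 13.5% | 9% |
| 30% vs 40% | 38% | 20% |
| 30% vs 45% | 69% | 39% |
| 30% vs 50% | 91% | 60% |

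With all 180 per group and no change of status, the five figures are 5%, 17%, 51%, 84% and 98%.

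**Step 4: does restricting the denominator remove the artefact?** In Case B, among participants off target at entry, the expected proportion reaching target is 20% in both groups, so the false difference is zero.

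**The case against.** Four points on the other side have force.

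*The wording of c to f.* A reader might infer that every one of these outcomes is a pure follow-up level, so that an unchanged low PHQ-9 score is counted as improved. The text does not support that. Outcomes c and f ask for a reduction, so an unchanged value does not meet them. Improvement in nephropathy, hypertension or dyslipidaemia can naturally be read as applying only to people who have the condition. What stands is that c and f require no off-target start, and that d and e do not state their denominator. These readings leave outcome b untouched.

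*Adjustment and matching.* A reader might infer that chi-square is the whole plan. It is not: baseline adjustment is mentioned, continuous data will also be tested, and the design is called matched. But the adjustment is only a possibility, and no matching step or variable is described. Neither secures balance in the share at target.

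*The size.* A reader might take 69% as the expected error rate. It rests on a 15-point imbalance, no adjustment and no change of status over the follow-up. It falls to about 39% under the modest movement in Case B, and the true imbalance is unknown and could be nil.

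*Analysis-plan detail.* Denominators for secondary responder outcomes are often left to the analysis plan. That would answer a missing detail. Outcome b, however, is defined in the article, and the definition conflicts with its label.

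**Conclusion.** The point holds in limited form. Outcome b is badly defined: a level reached at follow-up is called improvement, and eligibility admits people already at that level. Outcomes d and e have an unclear denominator, and c and f can be met by a trivial fall in someone already below the cut-off. Outcome a is unaffected, and nothing here touches the primary outcomes.

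With clinic-based groups, an unadjusted default test and optional baseline adjustment, following the plan as written can report a baseline difference as a programme effect. Under the assumptions shown, a 15-point difference in the share at target gives a false positive in about 39% to 69% of trials instead of 5%, and a 5-point difference in about 9% to 13.5%. These figures show how the bias works. They do not estimate what this trial will find, because the article gives no baseline shares. The matter is worth correcting but affects secondary outcomes only.

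**What to change.** 1. For outcomes b to f, define each threshold improvement among participants who were off that target at baseline, in both groups, and state the denominator.
2. Report participants already at target at entry separately, as maintained or not maintained.
3. Make adjustment for the baseline value mandatory. For example, report an ANCOVA of the continuous 12-month value on its baseline value alongside each threshold result.

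The cost is wording, since baseline assessments are already planned. Some denominators shrink: with 126 per group and 30% vs 45% at target at entry, outcome b would be assessed in about 88 (126 × 0.70) and 69 (126 × 0.55) participants. The change removes this artefact only. Differences between clinics in severity among those off target, and other confounding from the non-randomised design, remain.
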